## Abstract

**Background:**

Chronic kidney disease (CKD) and end stage renal disease (ESRD) are steadily increasing in prevalence in the United States. While there is reasonable evidence that specific activities can be implemented by primary care physicians (PCPs) to delay CKD progression and reduce mortality, CKD is under-recognized and undertreated in primary care offices, and PCPs are generally not familiar with treatment guidelines. The current study addresses the question of whether the facilitated TRANSLATE model compared to computer decision support (CDS) alone will lead to improved evidence-based care for CKD in primary care offices.

**Methods/Design:**

This protocol consists of a cluster randomized controlled trial (CRCT) followed by a process and cost analysis. Only practices providing ambulatory primary care as their principal function, located in non-hospital settings, employing at least one primary care physician, with a minimum of 2,000 patients seen in the prior year, are eligible. The intervention will occur at the cluster level and consists of providing CKD-specific CDS versus CKD-specific CDS plus practice facilitation for all elements of the TRANSLATE model. Patient-level data will be collected from each participating practice to examine adherence to guideline-concordant care, progression of CKD and all-cause mortality. Patients are considered to meet stage three CKD criteria if at least two consecutive estimated glomerular filtration rate (eGFR) measurements at least three months apart fall below 60 ml/min. The process evaluation (cluster level) will determine through qualitative methods the fidelity of the facilitated TRANSLATE program and find the challenges and enablers of the implementation process. The cost-effectiveness analysis will compare the benefit of the intervention of CDS alone against the intervention of CDS plus TRANSLATE (practice facilitation) in relationship to overall cost per quality adjusted years of life.

**Discussion:**

This study has three major innovations. First, this study adapts the TRANSLATE method, proven effective in diabetes care, to CKD. Second, we are creating a generalizable CDS specific to the Kidney Disease Outcome Quality Initiative (KDOQI) guidelines for CKD. Additionally, this study will evaluate the effects of CDS versus CDS with facilitation and answer key questions regarding the cost-effectiveness of a facilitated model for improving CKD outcomes. The study is testing virtual facilitation and Academic detailing making the findings generalizable to any area of the country.

**Trial registration:**

Registered as NCT01767883 on clinicaltrials.gov NCT01767883

## Background

Chronic kidney disease (CKD) and end stage renal disease (ESRD) are steadily increasing in prevalence in the United States (US) [1]. In 2000, there were 26 million American adults with CKD, and this represented a 30% increase over the past decade [1]. The annual incidence of ESRD is projected to increase from its 2007 level of 111,000 to 143,000 by 2020, when the total US population of people with ESRD is expected be over 770,000 [2,3]. The aging of the population and the rising prevalence of obesity, hypertension, and type 2 diabetes—the major risk factors for CKD—contribute to this trend [4]. CKD is a serious condition; stage three CKD is associated with a five-year all-cause mortality rate of 24.3% and a five-year need for renal replacement of 1.3%. Stage four CKD is associated with a five-year 45.7% mortality rate and a five-year 19.9% requirement for renal replacement [5].

While there is reasonable evidence that specific activities can be implemented by primary care physicians (PCPs) to delay CKD progression and reduce mortality [6-12], CKD is under-recognized and undertreated in primary care offices [13-15] and PCPs are generally not familiar with treatment guidelines [13,14]. Even when diagnosed, CKD is a chronic condition that, like diabetes, is frequently associated with co-morbidities, making effective treatment difficult due to the complexity of care.

The reasons for the slow rate of progress in improving healthcare delivery, especially for chronic conditions such as CKD, are complex. Rogers [16], in his classic studies of diffusion of innovation, outlined several potential barriers to adoption of innovation in many industries. These included lack of time and monetary resources, as well as organizational inefficiencies [16]. The health sector has been notoriously slow to adopt new approaches to care [17]. Competing demands and time limitations often inhibit the ability of PCPs to adopt evidence-based preventive services and manage chronic diseases well [18,19], and it takes several years for known evidence to become common practice [20-22].

The Chronic Care Model has been widely accepted and utilized in primary care practices as a means of improving evidence-based care [23,24]. Computer decision support (CDS) tools generated through electronic medical records and middleware vendors have been one important element of this model as a solution to some of the problems of implementing evidence into practice. However, a review by Garg *et al.* found that while CDS improved physician behavior in 73% of the studies, clinical markers were only improved 42% of the time [25-31]. Peterson *et al.* developed a nine-point action plan, including CDS and practice facilitation for implementing the Chronic Care Model [32]. This plan is referred to as TRANSLATE. TRANSLATE stands for ‘set your **T**arget, use **R**egistry and **R**eminder systems, get **A**dministrative buy-in, **N**etwork Information systems, **S**ite coordination, **L**ocal Physician Champion, **A**udit and feedback, **T**eam approach, and **E**ducation’ [32]. The combined efforts of the TRANSLATE model were highly effective in improving diabetes care in a randomized control trial (RCT) involving 24 practices and 8,405 diabetic patients [32]. At 12 months, intervention practices had significantly greater improvement in achieving recommended clinical values for systolic blood pressure (SBP), Hemoglobin A1C (HbA1C), and LDL cholesterol than control practices. Control practices were provided with a report of their process and outcome measures at baseline and were encouraged to continue usual quality improvement but did not receive CDS at the point of care [32].

The current study addresses the question of whether an adaptation of the facilitated TRANSLATE model with CDS, compared to CDS alone, will lead to improved evidence-based care for CKD in primary care offices, thereby slowing the progression to ESRD and improving patient health outcomes. A cluster randomized design was chosen to minimize contamination across arms and due to the logistical impossibilities of separating out practice workflow by provider to provide CDS and/or practice facilitation for only some providers within the same medical practice.

### Specific aims

#### ***Specific aim 1***

Conduct a cluster randomized controlled trial of point-of-care CDS plus the full TRANSLATE model of practice change, versus CDS alone in promoting evidence-based care in primary care practices for all patients with an eGFR <60 and >15 ml/min/1.73 m^2^ confirmed with repeat testing over three or more months. (CKD stages three and four).

#### ***Hypothesis 1.1***

CDS practices using the TRANSLATE model will provide a greater degree of evidence-based guideline-concordant care for CKD than CDS-only practices.

### Specific aim 2

Conduct an intent-to-treat and process analysis between the CDS practices with facilitation versus the CDS-only practices of the clinical outcomes of CKD progression and all-cause mortality.

#### ***Hypothesis 2.1***

Patients with stage three and four CKD in facilitated practices will have slower CKD progression than patients in CDS-only practices.

#### ***Hypothesis 2.2***

Patients with stage three and four CKD in facilitated practices will have significantly lower all-cause mortality than stage three and four patients in CDS-only practices.

#### ***Hypothesis 2.3***

The process evaluation will determine through qualitative methods the fidelity of the facilitated TRANSLATE program; find the challenges and enablers of the implementation process, and the contextual factors that contribute to TRANSLATE decisions and strategies; and translate lessons learned into pragmatic ‘best practices’ for future facilitation and dissemination.

### Specific Aim 3

Conduct a cost-effectiveness analysis that will compare the benefit of the intervention of CDS alone against the intervention of CDS plus TRANSLATE (practice facilitation) in relationship to overall cost per quality adjusted years of life.

#### ***Hypothesis 3.1***

The intervention of CDS plus TRANSLATE is more cost-effective than the intervention of CDS alone.

## Methods/design

This protocol consists of a cluster randomized controlled trial (CRCT) followed by a process and cost analysis of the study. The intervention consists of providing CKD-specific CDS versus CKD-specific CDS plus practice facilitation [33] for all elements of the TRANSLATE model.

The study is being performed by the State University of New York – University at Buffalo (UB) in collaboration with the American Academy of Family Physicians National Research Network (AAFP/NRN) with primary care practices across the United States. Ethical approval was obtained by the Institutional Review Boards at both UB and AAFP/NRN for all aspects of the study.

### Recruitment and randomization procedures

#### ***Inclusion criteria for clusters***

Only practices providing ambulatory primary care as their principal function, located in non-hospital settings, employing at least one primary care physician, with a minimum of 2,000 patients seen in the prior year, are eligible. ‘Practices’ are defined as distinct office locations that belong to organizations with one or more practice sites. Candidate practices are drawn from members of the Distributed Area Research and Therapeutics (DARTNet) members. These members have point of care decision support for preventive care and multiple chronic diseases. CKD will be added to the chronic disease management reminder system.

#### ***Inclusion criteria for patients***

Patient-level data will be drawn from the population of all active patients at each practice and will include all patients diagnosed with stage three CKD. Patients are considered to meet stage three CKD criteria if at least two consecutive eGFR measurements at least three months apart fall below 60 ml/min. At the inception of the study, we used data from the preceding 12 months to identify eligible patients (eGFR <60 and >15 ml/min) with additional patients added to the analytical dataset as they meet study criteria. These criteria were also used to initiate the clinical decision support algorithms.

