#### ***Randomization protocol***

In cases where two or more selected practices were drawn from the same multi-practice organization, contamination was limited by checking for clinician overlap. If overlap was minimal, organization was used as a stratification variable; if overlap was potentially problematic in terms of contamination, practices were constrained to be in the same group. From the pool of available practices, pre-study information from electronic health record (EHR) data on baseline performance characteristics related to CKD or in general and variables which may influence outcome measures, including practice and patient panel characteristics as well as pre-study clinical measures were collected (full-time equivalent physicians, mean HbA1c, % diabetic, % stage four CKD, % of diabetics with HbA1c >9, mean GFR, mean SBP, % with SBP >130, % with SBP >140, % African American, % Hispanic, % uninsured) [34]. Stratification variables included geographic region and organization. All possible combinations of the 18 eligible practices into two groups of nine were generated [35] using the IML procedure in SAS [36], retaining order so that the first designated group would be assigned to the intervention, the remaining practices to controls (n = 48,620). Only randomizations that were balanced on stratification variables were retained (n = 1,728). For each randomization, a balance criterion (defined as the sum of squared differences on standardized variables between control and intervention groups) was computed. After examining the distribution of the balance criterion, a maximum allowable difference between the groups was established and an optimal set of randomizations identified (n = 136). From this set, one was chosen using a random number generator and practices were assigned to treatment or control arms. This process was repeated for the next group of seven practices, including a dummy practice in the randomization procedure to accommodate the uneven number of practices. The remaining practices will be randomized using the same protocol. As with all CRCTs, patients are not randomized *per se*; they are assigned to treatment conditions along with the medical practices in which they receive care.

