**TRANSLATE elements that will be used in both arms**	
**T**arget:	Common targets will be set for all practices and tracked through the CKD tool. The CDS-only practices will receive a quick reference guide for the treatment of CKD
**R**egistry and reminder systems	CINA created a CKD registry and will maintain it throughout the study period. Point-of-care decision support specific to CKD will be provided to practice staff and physicians prior to patient visits.
**A**dministrative buy-in	Obtain consent from each practice and all practice sites asked to identify a physician champion and site coordinator to oversee study implementation at their site.
**N**etwork Information systems	The information systems (EHRs and CDS) will be used to create system level reports across all practices.

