**TRANSLATE element that will be used only in facilitated CDS practices**	
**S**ite coordination	A site coordinator at each practice will assemble a quality improvement (QI) team that will meet monthly to review performance data regarding CKD. The site coordinator will also work with the clinicians and practice staff to implement workflow changes such as pre-visit planning, standing orders, and patient education materials to improve efficiency of disease management. In addition, the site coordinator will be in contact with the practice facilitator by videoconference for assistance and advice.
**L**ocal physician champion	This person will be the clinician leader and educator for other providers in each practice. Responsibilities will include supporting the site coordinator and the QI team. This physician will be in contact with the academic mentor for the practice regarding clinical questions about CKD and will participate in learning collaboratives with the site coordinator.
**A**udit and feedback	Practice, individual provider, and patient-level outcome reports for the intervention practices will be generated through CINA regarding the seven performance measures (BP, HbAIC, LDL, use of ACE/ARB, referral to a nephrologist, smoking cessation and avoidance of NSAID or Cox-2) and will be reviewed by the team. Reports will also be reviewed quarterly with the practice facilitator by videoconference. The videoconference will allow the facilitator to learn what worked in each practice and to share what other practices have implemented successfully.
**T**eam approach	A quality improvement (QI) team consisting of the local physician champion, site coordinator and nursing, front office, and administrative staff will meet monthly to review progress of the CKD project. Workflow changes will be recommended and tested.
**E**ducation	An educational program using academic detailing and practice facilitation and videoconferencing will be utilized to support the practices’ efforts. All facilitated practices will be assigned an academic practice mentor. This mentor will be available to the office physician champion and practice coordinator to answer any questions and discuss plans. The academic mentor will review the practice’s data and participate in a quarterly videoconference with either the study coordinator or the lead clinician to review progress on the project.

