#### ***Data analysis for hypothesis 2.2 (all-cause mortality)***

All-cause mortality will be confirmed using the National Death Index to determine the exact date of death. The outcome for the analysis will be time from baseline to death. Patients who are alive at the end of the study period will be censored at the end of the follow-up time. Assumptions of the proportional hazards model will be checked for each variable. Covariates will include baseline eGFR, defined as the mean of the last two eGFRs prior to study entry, as well as socio-demographic and clinical characteristics.

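### Patients join the analysis after their practice is randomised, on a repeat-testing rule that facilitation may influence, so the arms may be compared on differently selected patients

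*Protocol article*

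**What the plan says.** Under Inclusion criteria for patients, the article first fixes a prevalent group: "At the inception of the study, we used data from the preceding 12 months to identify eligible patients". It then opens the cohort, "with additional patients added to the analytical dataset as they meet study criteria". The entry rule is that "at least two consecutive eGFR measurements at least three months apart fall below 60 ml/min".

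Two other sections fit the reading that later entrants count in the main results. The analysis of hypothesis 1.1 lets a patient be scored on only the eligible part of a year. The power analysis sizes the smallest practice (200 patients) on CKD prevalence across the whole study.

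Practices are the randomised units, and for patients "they are assigned to treatment conditions along with the medical practices in which they receive care". Registry and reminders are in both arms (Table 1): "Point-of-care decision support specific to CKD will be provided to practice staff and physicians prior to patient visits". In facilitated practices only, the site coordinator also works with staff to "implement workflow changes such as pre-visit planning, standing orders, and patient education materials", alongside monthly quality-improvement meetings on CKD and an academic mentor.

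For mortality, time runs from baseline, and "Covariates will include baseline eGFR, defined as the mean of the last two eGFRs prior to study entry". The article does not say whether study entry is a practice date or a patient date. Aim 2 is described as intent-to-treat, without naming the patient set. Nothing in the article restricts the main comparison to patients identified before allocation.

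**The concern.** In a cluster trial, randomisation protects the comparison of patients whose membership was settled before allocation. Here membership keeps growing afterwards, and the gate is a second eGFR ordered in routine care. Staff cannot be unaware of whether they have a facilitator, and the Background calls CKD under-recognised, so there is room for detection to differ.

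If facilitated practices retest more people, they may confirm more mild cases. Those patients could carry a different goal score and lower mortality with no effect of facilitation on care. The constrained randomisation balanced pre-study panel measures such as mean GFR and the percentage at stage four. That balance cannot extend to patients selected later. For a late entrant the baseline eGFR may also post-date randomisation. If time zero were the practice start, such a patient would have had to survive to the second test in order to be counted.

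**Working it through.** **1. The plan's own figure.** Inputs from Power analysis: 18 practices per arm, 200 patients each, ICC 0.03, effect 0.18 SD. Two-sided alpha 0.05 is assumed, because it is not stated.

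- Design effect = 1 + (200 − 1) × 0.03 = 6.97.
- Effective n per arm = 3,600 / 6.97 = 516.5.
- Standard error = √(2 / 516.5) = 0.0622 SD.
- Power = 82.4% (normal) or 80.2% (noncentral t, 34 df). This agrees with the stated figure of more than 80%.

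**2. Form of the bias in the goal score.** Let p1 and p0 be the late-entrant shares in the facilitated and CDS-only arms, and δ1 and δ0 the mean score of late entrants minus that of prevalent patients. With no true effect, the expected arm difference is p1·δ1 − p0·δ0. It vanishes when both shares and both selection effects are equal. None of the four quantities is in the documents, so everything below is assumed.

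*Same late share f in both arms, late entrants differing between arms by d SD.* Bias = f × d. Type I error uses the standard error from step 1 (normal):

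| f | d | Bias (SD) | Share of 0.18 | Type I error |
|---|---|---|---|---|
| 0.2 | 0.1 | 0.02 | 11% | 6.2% |
| 0.3 | 0.2 | 0.06 | 33% | 16.1% |
| 0.4 | 0.3 | 0.12 | 67% | 48.7% |

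*Different late shares, same selection effect δ.* Bias = (p1 − p0) × δ. At 30% vs 20% and δ = 0.3 it is 0.03 SD. At 40% vs 20% and δ = 0.5 it is 0.10 SD.

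**3. Mortality.** Let r be the death rate of late entrants relative to prevalent patients, assumed 0.5. The null ratio is (1 − w1 + w1·r) / (1 − w0 + w0·r), where w1 and w0 are late entrants' shares of person-time, not of patients. If late entrants are followed half as long (assumption), w = 0.5p / (1 − p + 0.5p).

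- 30% vs 20% of patients: w = 0.15/0.85 = 17.6% and 0.10/0.90 = 11.1%. Null ratio = 0.912/0.944 = 0.965.
- 40% vs 20%: w = 25.0% and 11.1%. Null ratio = 0.875/0.944 = 0.926.

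Weighting by patient share instead gives 0.944 and 0.889, which overstates the effect when late entrants contribute less time. All four figures are unadjusted.

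**4. Does more testing change case mix?** An illustrative simulation had no treatment effect. It assumed true eGFR mean 68 (SD 12), slope −1.5 (SD 2) per year, measurement SD 5, and quarterly testing opportunities over three years. It did not remove patients already identified at the start, so it shows direction only.

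| Quarterly test probability | Meeting criterion | Mean true eGFR at entry | Mean slope per year |
|---|---|---|---|
| 0.25 | 26.1% | 51.7 | −2.08 |
| 0.375 | 33.6% | 52.8 | −2.07 |
| 0.50 | 37.6% | 53.7 | −2.06 |

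More testing admits more and milder patients. The mean slope hardly moves.

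**5. Power if the main set is restricted** (same method as step 1, t on 34 df):

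| Patients per practice | Design effect | Effective n per arm | Power |
|---|---|---|---|
| 50 | 2.47 | 364.4 | 65.6% |
| 100 | 3.97 | 453.4 | 75.0% |
| 150 | 5.47 | 493.6 | 78.4% |
| 200 | 6.97 | 516.5 | 80.2% |
| 400 | 12.97 | 555.1 | 83.0% |
| 715 | 22.42 | 574.0 | 84.2% |

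**The case against.** The strongest reply is that the article never says facilitation targets eGFR testing. The seven audited measures in Table 1 are blood pressure, HbA1c, LDL, ACE/ARB use, nephrology referral, smoking and NSAID avoidance; eGFR testing is not among them. The workflow changes are described as serving disease management, not detection. Registry, reminders and decision support are common to both arms. Eligibility is a numeric rule applied to records, not a recruiter's judgement, and "These criteria were also used to initiate the clinical decision support algorithms", so the CKD prompts begin only once a patient already qualifies. Patients found at inception come from prior data and are largely unexposed. An open cohort is also a legitimate target for an intervention on practices. The mortality model adjusts for baseline eGFR, and the unseen analysis plan may settle the patient set.

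Much of this stands. It rules out reading the article as showing that facilitation does change who is confirmed; no testing rates by arm are given. It does not remove the route: standing orders, pre-visit planning and monthly CKD review can plausibly alter retesting, and the rule that admits later patients is stated, not omitted. Adjusting for an eGFR that may itself have been measured after allocation need not repair the selection.

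A reader might also infer that the intent-to-treat label in Aim 2 fails. It does not: analysing patients under their practice's allocation is intent-to-treat at cluster level. The problem is selection into the set, not departure from allocation.

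**Conclusion.** The open-cohort rule creates a risk of post-randomisation identification bias, and the article states no safeguard. The supported conclusion is that the arms may be compared on differently selected patients. The risk is confined to late entrants and is clearest for the goal score and mortality.

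Its size cannot be derived from the documents. Under the assumptions shown, the spurious score difference ranges from negligible (0.02 SD, type I error 6.2%) to serious (0.12 SD, 48.7%), and the null mortality ratio is about 0.93 to 0.97 after allowing for shorter follow-up. If testing does not differ by arm, this bias is zero.

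A reader might extend the point to a distorted eGFR slope under hypothesis 2.1. Nothing in the documents supports that, and in the simulation the mean slope barely changed. The matter should be fixed, with moderate confidence; it does not invalidate the trial.

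**What to change.** For hypotheses 1.1, 2.1 and 2.2, define the main analysis set as patients who met the eGFR criterion in the 12 months before their practice's randomisation date, with baseline values from that window. The cut-off must be randomisation and not the start of the intervention: by the Recruitment section, the second wave was already randomised while its intervention was still to begin in June 2013. A window ending at the start could still admit tests done after allocation.

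Analyse all patients, later entrants included, as a secondary analysis, with each late entrant's own entry date as time zero (delayed entry). Report eGFR testing rates and the number identified per 1,000 active patients by arm, so that readers can judge whether identification differed.

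This needs wording only, since the data come from records already being collected and Trial status says analysis has not begun. The costs are fewer patients in the main set and less information on incident CKD. The planned minimum of 200 already counts patients accrued during the study, so the smallest practices would fall below it. If every practice were that small, power would slip under the stated 80%: about 78% at 150 per practice and 75% at 100. It would fall to about 66% if only 50 were prevalent. At the expected 715 it is about 84%, and still 83% at 400.
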